## Abstract

University students often face significant mental health challenges, including depression, anxiety, and difficulties in adjustment, which can be exaggerated by the demands of independent living and increased life responsibilities. These challenges are often compounded by barriers to seeking help, such as stigma and limited access to university resources, which can further deteriorate students' well-being. This protocol was created to assist college students in overcoming these obstacles and to assess, in comparison to a control group, the impact of a guided and unguided online intervention platform based on transdiagnostic CBT (UNIPDES) on depression, anxiety, and adjustment levels. The calculated sample size for the study will include 330 students, and the participants will be selected from five different universities located in Türkiye. Participants will be randomly assigned to either guided, unguided, or control groups. Guided and unguided group participants will receive six weeks of intervention, and the waitlist control group will receive the unguided version of the program after twelve weeks of randomization. Assessments will take place at baseline, post-test (8 weeks post-baseline) and follow-up (12 weeks post-baseline). A Mixed ANOVA will be employed to analyze the data, with Group (Guided, Unguided, Control) as the between-subjects factor and Time (Baseline, Post-Test, Follow-Up) as the within-subjects factor, as well as to assess the interaction effect between Group and Time on the primary outcomes—changes in depression, anxiety, and adjustment levels. Additionally, students’ reasons for dropout will be assessed qualitatively. The results from this study can build evidence for the effectiveness of transdiagnostic guided and unguided internet-based intervention for treating depression, anxiety, and adjustment problems of students. UNIPDES can provide a flexible, easy-to-access, and cost-effective treatment for the problems that students commonly face. Trial registration is registered at ClinicalTrials.gov Protocol Registration and Results System (Trial number: NCT06245200).

## Introduction

1

The university years represent a shift from youth to adulthood and are characterized by increased independence in handling life's challenges and making decisions which leads to heightened emotions of responsibility and the need to make decisions about potential romantic partners and career possibilities [1]. Owing to developmental alterations in several spheres of life, these years are crucial for people's mental and overall well-being [2] and also critical for marking the onset of several mental health problems [3,4]. Previous studies [3,[5], [6]] have shown that university students deal with a range of challenges in their personal, professional, academic, and social lives and these are found to be closely related to several mental health issues, especially stress, anxiety, and depression. According to a survey, students who were having trouble adjusting to school, managing their workload, their mental health, and their requirements for development were the main reasons they were reaching out to the university's counseling services [7].

A growing number of university students are experiencing psychological problems [[8], [9], [10]] and these have been increasing exponentially over the years [11,12]. These psychological problems especially affect students in the academic field [13,14] and are closely related to higher dropout rates [5].

A number of contextual and personal factors were involved when discussing university students' mental health. Byrd and McKinney [15] found that improved coping skills, communication skills, a strong spiritual identity, academic self-confidence, heterosexuality, intergroup awareness, social bonds, and satisfaction with the school have a positive impact on college students' mental health. Suicidal thoughts, difficulty balancing work and school, a negative disposition toward the university environment, and less engagement with instructors were, nonetheless, linked to poor well-being. Similarly, in their systematic review, Campbell et al. [16] found that several factors such as sexual orientation, ethnicity, gender, previous mental health problems, childhood traumas, previous experiences with parents (i.e., overcontrolling parenting), and having a disability were related to poor mental health, whereas optimism, mental health literacy, having strong social support, participation in learning, good experiences and involvement in lectures, and self-efficacy were associated with better mental health.

Although university students often experience psychological problems, they are reluctant or unable to seek professional help for various reasons, such as a sense of self-sufficiency, fear of stigma, or privacy concerns [17]. On the other hand, insufficient resources of university counseling centers cause long waiting lists for students seeking help [18]. When these elements are evaluated together, there is a need for alternative options that are permanent, appeal to students, can reach large audiences, and can eliminate the obstacles that university students face in seeking psychological help.

### Internet-based interventions for mental health

1.1

Internet-based interventions can be either unguided (self-directed, without input from a therapist) or guided (with varying degrees of therapist contact). These programs are designed to raise awareness of psychological issues and provide guidance, treatment, and support to individuals suffering from various psychological problems ([19,20] Digital Health, 2022). Recent experimental studies have shown that internet-based interventions are useful for a variety of problems, including depressive mood [21,22], stress management [23], social anxiety [24,25], obsessive-compulsive disorder [26,27], substance and alcohol use [28,29], and suicide prevention [30]. Previous studies on the effectiveness of internet-based interventions with university students also showed promising results in reducing problematic internet use [31], alcohol and drug addiction [32,33], and depressive mood and anxiety [34]. The abovementioned studies either have guided and unguided groups and control group, or one group (i.e., guided) and control group when comparing the effectiveness of internet-based interventions, and the effectiveness of the internet-based interventions were evaluated over participants’ improvements on measured problem areas. The results, overall, suggested that internet-based interventions can be as effective as traditional therapies in decreasing symptoms on problem areas. When the literature has been examined regarding the differences in effectiveness of guided and unguided methods of delivery of internet-based interventions, an umbrella review of meta-analyses by Zhang and colleagues [35] reported that the results of guided interventions typically demonstrate more effectiveness than unguided ones.

Internet-based treatments offer several benefits, such as being accessible at any time or place, lowering stigma by preserving anonymity, lowering the need for trained specialists and associated costs by reaching many people at once, and letting individuals move at their own pace. It is clear that internet-based interventions are preventive in the sense that they provide information about mental health, encourage help-seeking, reach a large number of people at once, reduce the symptoms of the individual's mental health problem, increase their well-being, and prevent mental disorders from persisting in the future [36]. Besides their advantages, dropout rates denote a significant challenge which reduces their effectiveness and sustainability (e.g., Ref. [37,38]). Therefore, understanding the attitudes towards internet-based interventions is crucial due to their effects on dropout rates. Specifically, understanding how positive or negative attitudes influence individuals' decisions to adhere to or discontinue such interventions can provide valuable insights for improving the design and implementation of these approaches.

One of the main sources that students get psychological help is the guidance and counseling centers (GRC) of the universities (i.e., [39]). In Türkiye, the guidance and counseling services in universities has begun for the first time in 1973 by a higher education law number 1750. In 1982, by another law, universities have been obligated to establish GRCs [40]. University GRCs includes professionals from psychiatry, counseling, psychology and social work and these centers provides variety of services (i.e., individual counseling, group counseling, consultancy), and one of the biggest concerns of staff working on these GRCs is the work overload [41]. On the other hand, internet-based interventions are a relatively new field of study in Türkiye. Previous research on this area consisted of compilations and reviews [42,43]. Several internet-based intervention programs included an unguided self-help program for psychological symptoms during COVID-19 [44,45], cognitive distortions and psychological symptoms for children [46], dealing with COVID-19 distress [47], obsessive-compulsive disorder [48,49]. In all these interventions, a rather limited/moderate sample size was used.

The transdiagnostic approach (TA) focuses on the common psychopathological processes that underpin the development and persistence of mental disorders. Even if various problems are classified differently, it is possible to discern how they overlap or differ from one another, and TA tries to treat mental disorders based on these overlapping elements [50]. TA has a flexible and modular structure that allows it to be easily integrated into the cognitive behavioral therapy (CBT) process [51,52]. Transdiagnostic treatments in CBT include universal strategies that can be used across problems. Several strategies, thus, utilized within TA includes targeting explicit selective memory, emotional inference, repetitive negative thinking style, emotional attention to external and internal stimuli, attention focused on avoidance and security, positive and negative metacognitive beliefs, avoidance behaviors, safety seeking behaviors, and experiential avoidance [53,54]. TA, therefore, is a framework for doing therapy in a transdiagnostic and effective manner, while others are disorder-specific. Its clarity, simplicity, and focus on commonality make it effective in treating comorbidities and addressing various problem areas [55].

Previous studies showed the effectiveness of internet-based TA intervention on people with anxiety and depression [[56], [57], [58]], sleep-related problems for adults and adolescents [59], and studies with college samples found that TA-based internet-based interventions were effective in treating underlying personality risk factors [60], depression [34], anxiety and depression [61]. All these programs were presented with a guide (rather than self-help only). Even if follow-up studies showed that the benefits of interventions persist [61], the literature also states the requirement for further research to identify the mechanism behind their effectiveness [62].

### Aims

1.2

This study aims to accomplish two main objectives. The initial goal is to test the effectiveness of the internet-based intervention for university students, UNIPDES, which is based on a transdiagnostic CBT, in raising psychological adaptation levels and improving the depressive and anxiety symptoms in university students, controlling for participants' initial depressive symptoms, anxiety, psychological adjustment scores, and attitudes toward internet-based interventions. Consistent with this objective, we seek to evaluate the variations between guided and unguided treatment delivery compared to the waiting list control group.

The second goal is to assess the reasons why users who enroll in internet-based interventions dropout. In order to assess the possible influence of participant attitudes on internet-based therapies on dropout rates, we want to incorporate an analysis of these attitudes into our study. In particular, knowing how people's attitudes, whether favorable or unfavorable, affect their choices to stick with or stop using such interventions can help a researcher to improve their design and execution. Our study aims to add to the body of knowledge on dropout in internet-based interventions in this regard.

## Methods

2

### Study design

2.1

This project was designed as a mixed methods study to investigate the impact of an online intervention program based on the transdiagnostic CBT on university students' levels of psychological adaptation, reduction of depressive mood, and anxiety symptoms, as well as the durability of these effects [63]. The rationale behind utilizing a mixed method is typically that combining qualitative and quantitative data yields a more comprehensive grasp of the study problem than each approach could on its own [64]. Developing an online intervention platform based on transdiagnostic CBT (UNIPDES) and evaluating its effectiveness are the primary objectives of the research. The clinical Research Ethics Committee of the third author's university approved the study protocol (approval number E−80558721-050.99-2300154653), information booklet, and informed consent form. The trial is registered on clinicaltrials.gov (Trial Number:NCT06245200) and the CONSORT chart (Fig. 1) was presented on how the study is conducted and reported.

**Fig. 1 fig1:**
[figure not shown]
Consort flow-chart of the study.

### Participants

2.2

Participants in this study will be composed of students from five different universities located in Türkiye. All these universities are public universities, and they range from small (around 5000 students) to large scale (around 1.000.000 students) based on their student numbers. Participants who took part in the quantitative study will also be the ones chosen for participation in the qualitative part. The following inclusion criteria will be used for participation: a) volunteering to participate in the study; b) having a valid e-mail address; c) having internet access (computer or mobile device); d) being over the age of 18; e) not receiving any ongoing psychological support during the research period; and g) scoring less than 15 on the Patient Health Questionnaire 9 (PHQ-9) and less than 14 on the Generalized Anxiety Disorder-7 (GAD-7) scales.

In line with our aim of developing a preventive program (UNIPDES) designed for a broader audience, the majority of participants in our study are university students and do not represent a clinical sample. Only individuals with severe problems were excluded from the study, as these individuals are more appropriate for individualized psychological counseling for their needs than internet-based interventions. Therefore, this study aims to reach a heterogeneous sample, which results in addressing the needs of a wider population and creating a program with preventive and protective features.

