### Procedure

2.3

Posters and online announcements of the study will be created and sent to the five universities mentioned above. The project website, advertising posters, academic institutions' websites, and social media sites will all be used to announce the study. Students will be able to navigate to the project website by scanning the QR code on the posters.

Upon accessing the project website, participants will be asked to complete an online informed consent form outlining the study's aims before deciding whether to volunteer. After obtaining the participants' consent to volunteer in the study, they will be requested to fill out the questionnaires. Those who meet the remaining inclusion requirements but score highly on PHQ-9 and GAD-7 or undergoing psychological treatment will not be able to register or access the system. These users will be notified to seek professional help if they so choose, along with a window with contact details for resources (counseling center of the university, medico-social units) that will enable them to receive help at the appropriate university. Allotted participants will get e-mails and SMSs letting them know which group they are in. To guarantee the validity and reliability of our results, we want to take this heterogeneity into consideration during our analysis procedures. The consort flow chart of the study is presented in Fig. 1.

In the qualitative part, to ensure diversity in the semi-structured interview process, participants who discontinued the program with the lowest and highest symptom levels will be invited, while maintaining a balanced gender ratio. This stratified approach aims to capture a wide range of perspectives. The interviews will be conducted by researchers holding doctoral degrees in psychology, ensuring both expertise and consistency in data collection.

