### Control condition

2.8

The waitlist control (WLC) group will be asked to complete pre- and post-assessments at initial registration and by the end of the eighth week. Participants will not be in contact with the research team throughout the waiting period. They will be given the unguided version of the program at the 12th week, after the completion of the assessment tools. Participants who complete all measurement tools will receive a gift card (which they can spend on numerous web pages) as a means of encouragement.

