### Statistical analyses

2.10

A Mixed ANOVA will be employed to analyze the data, with Group (Guided, Unguided, Control) as the between-subjects factor and Time (Baseline, Post-Test, Follow-Up) as the within-subjects factor. This approach will assess both the main effects of Group and Time, as well as the interaction effect between Group and Time on the primary outcomes—changes in depression, anxiety, and adjustment levels. Post-hoc tests will be conducted to explore significant interactions. If necessary, covariates will be included in the analysis through a Mixed ANCOVA to adjust for baseline differences.

Dropout and missing data are anticipated in the study. To address this, missing data will be handled using relevant methods, e.g., multiple imputation or Multilevel Mixed-Model Regression Analysis, depending on the nature and pattern of missingness. Multiple imputation will be employed to estimate missing values if the data are missing at random, while Multilevel Mixed-Model Regression Analysis will be applied to account for both missing data and repeated measures over time. Baseline characteristics across the three groups will be tested using statistical methods such as t-tests, chi-square tests, or ANOVA to ensure comparability. Any significant differences will be adjusted for in subsequent analyses. These approaches will help ensure the robustness of the findings despite anticipated dropout and missing data.

The qualitative data will be transcribed and coded into themes by two independent researchers to ensure reliability. In the analysis of the data, the MAXQDA program will be utilized. According to the principles of [81] to ensure the reliability and validity of the results, the coding and assignment of themes will be conducted by several researchers, and the evaluation will be made through consensus/(disagreement + agreement) ∗100 formula as suggested. At the end of the analysis, consensus and disagreements will be evaluated in a project team meeting.

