## Discussion

3

The purpose of this study protocol is to outline the randomized controlled study design, which assesses the effectiveness of both guided and unguided online intervention platform based on transdiagnostic CBT (UNIPDES) on the levels of psychological adaptability, anxiety, and depressive mood in university students. It is anticipated that the participants displaying anxiety, depressive symptomatology, and challenges with psychological adaptation will benefit clinically significantly from the UNIPDES (either guided or unguided) in comparison to the waitlist control group. While the primary focus of the UNIPDES program is to provide clinical benefits for participants displaying anxiety, depressive symptomatology, and challenges with psychological adaptation, we also anticipate that participants without symptoms will experience positive outcomes. For these individuals, the program is expected to serve a preventive function, enhancing psychological resilience and promoting adaptive coping strategies for future stressors. By targeting a heterogeneous sample, we aim to evaluate the program's effectiveness not only in reducing existing symptoms but also in fostering psychological well-being and prevention among symptom-free participants. These distinctions will be considered in our analysis to assess the program's impact across different participant profiles. Furthermore, the investigation of the therapeutic implications of the effectiveness of two distinct intervention levels of guidance -guided and unguided - will enhance the value of the study.

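### The readings that screen out high scorers also serve as T0, so the Time main effect and any within-arm change from T0 are biased toward worsening on PHQ-9 and GAD-7; the between-arm comparisons are not

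*Protocol article*

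**What the plan says.** **Entry.** Protocol article, section 2.2, requires "scoring less than 15 on the Patient Health Questionnaire 9 (PHQ-9) and less than 14 on the Generalized Anxiety Disorder-7 (GAD-7) scales". No lower limit is given, and the Discussion expects symptom-free students to take part: "we also anticipate that participants without symptoms will experience positive outcomes".

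**When the scores are taken.** Section 2.3: "After obtaining the participants' consent to volunteer in the study, they will be requested to fill out the questionnaires". High scorers "will not be able to register or access the system". Section 2.8 asks the waitlist arm to "complete pre- and post-assessments at initial registration" and, for the later assessment, at the end of week 8. Table 1 in section 2.9 lists PHQ-9 and GAD-7 at T0, T1 and T2 only, with no separate screening reading.

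**Randomization.** Section 2.4 assigns students to arms after they have registered and met the entry criteria.

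**Analysis.** The abstract has "Time (Baseline, Post-Test, Follow-Up) as the within-subjects factor". Section 2.10, on the primary outcomes: "This approach will assess both the main effects of Group and Time", together with their interaction. Post-hoc tests follow a significant interaction; their form is not specified.

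**The concern.** A single PHQ-9 or GAD-7 reading is part stable level and part fluctuation on the day. An upper limit removes students who read high that day and keeps those who read low. If the limit acts on T0 itself, the T0 mean of those kept is too low. With a retest correlation below 1 and no true change, their mean must then rise at T1 and T2. The Time main effect has T0 as one of its levels, so it mixes this selection effect with real change.

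Two things are at stake. A stated test on primary outcomes does not keep its 5% error rate as a test of no change. And the Discussion holds that for symptom-free students "the program is expected to serve a preventive function", so an upward course in the waitlist arm could be described as deterioration when part or all of it comes from screening. Section 2.10 does not guard against this. The only control-arm trend that the article mentions, among the limitations in the Discussion, is minor improvement, which is the opposite direction.

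**Working it through.** **The plan's own figure.** The article gives no figure for this drift. Its sample size of 244 (section 2.5) reproduces as an ANCOVA F test with three groups, four covariates, alpha 0.05, power 0.80 and f = 0.2 (power 0.8001). The printed f = 2 does not reproduce it; that is a separate matter. It matters here because 244 is used below, and because it shows that the sizing effect is a between-group one.

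**Inputs.** From the article: the two limits, 35% dropout, and 330 students, which leaves 330 x 0.65 = about 214 complete cases. Assumed, because the article gives none: before screening, PHQ-9 mean 7-10 and SD 5-6; GAD-7 mean 6-8.5 and SD 4.5-5.5; correlation between the scales 0.7; retest correlation r 0.5-0.8; no true change.

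**One limit, normal scores.** Expected rise = (1 - r) x SD x phi(a)/Phi(a), with a = (14.5 - mean)/SD. It is positive for every r below 1. For mean 9 and SD 5.5:

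- a = 5.5/5.5 = 1, and phi(1)/Phi(1) = 0.2420/0.8413 = 0.2876
- T0 mean after screening = 9 - 5.5 x 0.2876 = 7.42, with 16% screened out
- rise at r = 0.7: 0.3 x 5.5 x 0.2876 = 0.47 points; at r = 0.5, 0.79; at r = 0.8, 0.32

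**Both limits, simulated rounded scores.** Chance of a significant rise from T0 when nothing changed:

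| Score shape, PHQ-9 mean, r | Screened out | PHQ-9 rise | SD of change | One arm, n = 81 | Pooled, n = 244 |
|---|---|---|---|---|---|
| Normal, 7, 0.8 | 9% | +0.17 | 2.96 | 0.07 | 0.14 |
| Normal, 9, 0.7 | 21% | +0.55 | 3.95 | 0.24 | 0.58 |
| Skewed, 9, 0.7 | 20% | +0.64 | 3.69 | 0.35 | 0.78 |
| Skewed, 10, 0.5 | 26% | +1.35 | 4.96 | 0.69 | 0.99 |

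The first and last rows are the extremes of the range examined. GAD-7 rises by +0.14 to +1.14. Check of the first row: 0.17/(2.96/√244) = 0.90, and the normal upper tail beyond 1.96 - 0.90 = 1.06 is 0.14. These are rejections in one direction of a two-sided 5% test, where 2.5% would be nominal.

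**The Time F test itself.** In 1500 simulated trials per setting, with N = 214, three equal arms, PHQ-9 mean 6-9 and r 0.6-0.8, the test rejected in 25% to 92% across seven parameter sets. A further simulation with n = 213 gave 18% to 92%, while Group x Time stayed at about 6%.

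**Between arms.** In 2000 simulated trials of 330 students (PHQ-9 limit only, r = 0.6), the mean change over time was +0.64, while the between-arm difference in change was 0.02 with simulation standard error 0.014, consistent with zero.

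**With true benefit added.** Take a drift of 0.66 and assumed gains of 2 and 1 points in the two program arms. The average change is 0.66 - (2 + 1 + 0)/3 = -0.34, a net improvement smaller than the true average of 1 point.

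**The case against.** **No sentence says that the screening score is T0, and the flow chart is not shown.** True. But the described sequence has one round of questionnaires before registration, a pre-assessment at registration and no other baseline. If a separate baseline is in fact taken after screening, the point largely falls away.

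**The size is all assumption.** Also true. The article gives no mean, SD or retest correlation. Students who answer posters when distressed may improve on their own, so the net direction of change is unknown. What does not depend on the chosen values is that the selection itself pushes upward.

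**The effectiveness question is untouched.** This stands. The Aims and Discussion judge the program against the waitlist, and screening comes before randomization, so every arm has the same expected drift. A reader might infer that the treatment comparison is biased; the design does not support that. Nor would flat program arms beside a rising waitlist be a false effect: with equal drift, that gap is a real between-arm difference. Only the word deterioration, applied to the waitlist, would be unsafe. For the same reason the drift should not be expressed as a share of the effect size used for sizing, which is a between-group quantity.

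**Within-arm tests are not named, and BASE-6 has no limit.** Both stand. Section 2.10 names only unspecified post-hoc tests, and the one stated use of individual pre-post differences is to choose interviewees (section 2.9.2.4). BASE-6 is affected only through its correlation with the two screened scales.

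**A condensed article leaves interpretation to the full plan.** This does not remove the point, because section 2.10 itself states the Time main effect as something to be assessed on the primary outcomes.

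**Conclusion.** The concern holds for the Time main effect over T0, T1 and T2 and for any within-arm change from T0, on PHQ-9 and GAD-7. Under the assumed distributions the drift is roughly +0.2 to +1.4 PHQ-9 points, and a test of no change rejects in about 14% to over 90% of trials. The figures depend on the assumed means, SDs and correlations and on the inference that the screening reading is T0.

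A reader might go further and conclude that the trial will show a worsening. The documents do not support that. Under mild assumptions (normal scores, PHQ-9 mean 7) the pooled rise is significant in only 14% to 32% of trials at n = 244, and true gains or natural recovery can outweigh the drift, which then hides part of the improvement. This is worth correcting because a stated test is biased and the remedy is cheap; it does not threaten the randomized comparison.

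**What to change.** In section 2.10 and the abstract:

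- Keep Time in the model, but do not test or interpret its main effect over T0, T1 and T2, or within-arm change from T0, as evidence of change.
- Base statements on effectiveness, prevention and durability on Group x Time and on baseline-adjusted between-arm differences at T1 and T2. The Aims already intend to control for initial scores.
- State that a rise from T0 in the waitlist arm will not by itself be read as deterioration.

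The entry limits stay as they are. A T1-to-T2 test is not a fully clean substitute: in one simulated setting the drift was +0.59 at T1 and +0.68 at T2, so a small residue remains.

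The cost is wording only, with no new data or participants. The small downside is that the customary pre-post Time test is no longer reported as a finding.
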